#### Duration of untreated illness (DUI)

The DUI is understood as the number of months between illness onset and the initiation of an ED-specific treatment. Onset of the disease is conceptualized as the first occurrence of all symptoms of typical or atypical AN as described above.

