#### Control variables

The questionnaire includes sociodemographic and control variables, such as age, gender, marital status, educational level, migration background, housing situation and occupational activity. At post assessment, patients are asked to indicate any contact with parts of the systemic interventions from *psychenet*. In case of positive response, further questions clarify which of the ED-specific interventions were recognized and if treatment initiation is subjectively eased by these interventions.

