### Sample size/power calculation

Based on former international studies [25] with an average DUI of 19 months and an effect size of 0.4, we considered a DUI reduction of 4.8 months or 25% as clinically relevant. Thus, for a two-sided type-I error of 5% two samples with 100 participants each are needed to reach statistically significance with a power of 80%.

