### Statistical analyses

In order to test the primary hypotheses regarding change vs. no change from pre to post assessment univariate multiple regression analysis with the dependent variables DUI and DUC as well as the independent variable period of assessment will be conducted. Additionally, recruitment setting will be included as random control variable whereas age and contact with the systematic intervention will be taken into account as a fixed control variable. Statistical significance will be taken two-sided p <0.05 throughout and regression coefficient with 95% confidence intervals (CI) will be used to express the uncertainty in the data.

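### The age covariate in the primary model appears to be age at the survey, which contains DUI; this distorts the period effect (a 4% to 20% shrinkage under stated assumptions), and age at onset should replace it

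*Protocol article*

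**What the plan says.** The primary analysis is a regression of DUI, and of DUC, on the period of assessment, with recruitment setting as a random term. On the fixed covariates, the Statistical analyses section says "age and contact with the systematic intervention will be taken into account as a fixed control variable". It does not say at which time point age is taken.

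The only age variable described stands under Control variables: "The questionnaire includes sociodemographic and control variables, such as age, gender, marital status" and further items. Under Inclusion and exclusion criteria, participants must at that time be in their first ED-specific treatment or be clients of an ED-specific counselling center. Under Recruitment, the practitioners there hand out the questionnaire.

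The outcome is defined so: "The DUI is understood as the number of months between illness onset and the initiation of an ED-specific treatment". Under Variables and instruments, onset is asked in the questionnaire and checked in the telephone interview, so age at onset could be derived. It is not named as a covariate.

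The case for adjusting for age rests on the Background and Study hypotheses sections, which treat age as an individual factor related to duration of illness, with longer illness in older women.

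**The concern.** For a patient surveyed during her first treatment, age at the survey is a sum: age at onset, plus DUI, plus time already spent in treatment. This follows from the definitions.

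Two consequences follow. Part of the outcome stands among the regressors. And the covariate responds to the intervention: if DUI is shortened, a post-period patient with a given onset age is younger when surveyed. Comparing pre and post patients of equal current age then compares patients whose onset ages differ, and some of the intervention effect is credited to age.

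At stake are the primary estimate, its confidence interval and its power. The design is sized for 80% power with almost nothing to spare. DUC is exposed in the same way, because age at the survey also contains DUC.

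**Working it through.** **Inputs from the Protocol article (Sample size/power calculation).** The section starts "with an average DUI of 19 months and an effect size of 0.4", continues "we considered a DUI reduction of 4.8 months or 25% as clinically relevant", and concludes that "for a two-sided type-I error of 5% two samples with 100 participants each are needed" for 80% power. The implied DUI SD is 4.8 / 0.4 = 12 months.

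**Assumptions, not in the article.** SD of onset age: 24, 36 or 60 months. SD of time in treatment: 3 months. Onset age and time in treatment have the same distribution in both periods. Onset age and DUI are independent, unless a correlation is given.

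**Step 1: reproduce the sample size.** n per group = 2 × (1.96 + 0.842)² / 0.4² ≈ 98.1, so 99; the t-test version gives 99.08, so 100. Power at 100 per group is 0.807 (normal) or 0.804 (t). The stated figure is not in dispute.

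**Step 2: bias formula.** Write current age as A = O + D + T (onset age, DUI, time in treatment). With A in the model, the period coefficient is the pre-post difference in D minus b times the difference in A, where b is the within-period slope of D on A. If only DUI changes between periods, both differences are −4.8, so the coefficient is −4.8 × (1 − b).

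Under independence, b = 12² / (SD_O² + 12² + 3²) and the residual SD is 12 × √(1 − b). The standard error is 12 × √(1 − b) × √(2/100) × √(1 + 5.76 / Var(A)). The last factor allows for the correlation between period and age, with 5.76 = 4.8² / 4.

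**Step 3: results under independence.**

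| Onset-age SD | b | Period coefficient (months) | Power |
|---|---|---|---|
| 60 months | 144 / 3753 = 0.038 | −4.62 | 0.79 |
| 36 months | 144 / 1449 = 0.099 | −4.32 | 0.76 |
| 24 months | 144 / 729 = 0.198 | −3.85 | 0.71 |

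**Step 4: simulation check.** 2000 trials per setting, 100 per group, gamma-distributed DUI with means 19 and 14.2 and SD 12, exponential time in treatment with mean 3 months.

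| Onset-age SD | Adjusted for current age: coefficient, power | Adjusted for onset age: coefficient, power |
|---|---|---|
| 60 months | −4.63, 0.78 | −4.76, 0.80 |
| 36 months | −4.35, 0.75 | −4.79, 0.80 |
| 24 months | −3.85, 0.70 | −4.80, 0.81 |

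**Step 5: direction.** With correlation ρ between onset age and DUI, the numerator of b is 12² + ρ × SD_O × 12. It is zero at ρ = −12 / SD_O: −0.50, −0.33 and −0.20 for onset-age SDs of 24, 36 and 60 months. At SD 36 the coefficient is −4.12 for ρ = 0.2, −4.32 for ρ = 0, −4.58 for ρ = −0.2 and −5.14 for ρ = −0.5. The last is a bias away from zero.

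**The case against.** **The article says only age.** That it means age at the survey is an inference, and a condensed article may leave a covariate's reference point to the analysis plan. The inference is strong, though. The article itself names the covariate, describes only one age, lists it under the same control-variable label, and places its collection after DUI has ended. If onset age was meant, a short clarification settles the matter.

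**The direction is conditional.** A reader might infer that the effect is always biased towards zero. The article gives no correlation between onset age and DUI, and Step 5 shows where the sign flips. The relation the article invokes, longer illness at older age, points towards shrinkage. But it is reported for duration of illness, not DUI, and the cited study is not at hand. So one cannot say how much of that finding comes from the same identity.

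**The size is modest at the article's own SD.** A reader might infer losses of a third to a half. With a DUI SD of 24 months, leaving time in treatment aside, b = 576 / (576 + 1296) = 0.31 for an onset-age SD of 36 months, and 0.50 for 24 months. Power would be about 65% and 51% in a design sized for 80% at that SD. The article supports neither that SD nor that design. With 100 per group and SD 24, power for 4.8 months would be about 29% before any age adjustment, and the SD would be the main problem. There is also no upper age limit, so onset ages may be widely spread, which makes the loss smaller.

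**No false benefit is created.** If onset age and time in treatment are balanced between periods and the intervention does nothing, this mechanism adds no bias. That stands.

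**The Discussion concedes that confounding is hard to control.** It does, but it does not mention this mechanism, which the planned analysis itself would introduce.

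**Conclusion.** The point holds in a conditional and moderate form. On the article's own description, the age covariate appears to be age at the survey, which contains DUI and is changed by the intervention. The period coefficient then does not estimate the change in DUI between periods.

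With a DUI SD of 12 months, independent onset age and assumed onset-age SDs of 5 to 2 years, the effect shrinks by about 4% to 20% and power falls from about 80% to between 79% and 71%. A positive correlation increases the shrinkage at these SDs. A clearly negative one, beyond −12 / SD of onset age, reverses the bias. The onset-age SD and the correlation are not in the article, so the range is an illustration and not an estimate for this trial. For DUC the mechanism applies, but its size was not calculated.

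**What to change.** In the Statistical analyses section, replace age with age at illness onset as the fixed covariate in the DUI and DUC models. Derive it from the onset information asked in the questionnaire and checked in the telephone interview. If that was the intention, say so.

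The cost is a few words and one derived variable, with no new data. Age adjustment is kept, and the outcome no longer stands among the regressors.

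One caution: onset is recalled, so an error in its date enters both DUI and onset age, with opposite signs. This does not shrink the period coefficient while onset ages are balanced between periods, so onset age should be tabulated by period.

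The same sentence also adjusts for contact with the intervention, which under Control variables is asked only at the post assessment. That is a separate over-adjustment and needs its own correction; changing the age variable does not remove it.

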## Discussion

This study is a pre-post study that examines the evaluation of a systemic public health intervention for EDs. The systemic intervention contains the establishment of a network of health care professionals within the area of EDs, the publication of a treatment guide for patients, relatives and therapists, the distribution of information concerning EDs by short-films and posters as well as the establishment of a special outpatient clinic. It is expected that the systemic intervention decreases the time between the onset of AN and the first contact with healthcare system as well as the beginning of an ED-specific treatment. It is further assumed that the systemic intervention reduces ED pathology and comorbidity at treatment initiation. Currently, there is no comparable intervention in the field of EDs.

The value of the intervention must be classified as high since a long DUI in AN is one of the strongest predictors of a poor outcome [16]. Evidence-based interventions (e.g. [47]) have to be initiated at an early stage of the illness to develop the full effectiveness. Reducing the DUI is one important step to improve patient flow into special health care in patients with AN. Moreover, the intervention plans to improve the networking of different instances of the health care system. Use of existing resources is increased, which could on a long-term basis lead to a reduction of the high costs for AN treatment [11]. At present, evidence-based treatments for AN [12] are not utilized sufficiently early and targeted [7,13,25,48].

The study aims to evaluate the systemic intervention, which is, next to the value of the intervention itself, of great interest for further public health interventions. Assessing the DUI and additionally the DUC may also lead to a better understanding of the period during the time until the first ED-specific treatment is initiated.

In spite of the huge demand for such evaluated interventions, some limitations to this study have to be mentioned: Since this project is a systemic public health intervention, the implementation of a Randomized Controlled Trial (RCT) is not feasible. Therefore, it is problematic to control confounding factors and make causal conclusions. However, this limitation can be attributed to the aims of the project, which leaves no option of implementing a RCT. Due to the complexity of the systemic intervention it is further not realizable to conduct a dismantling investigation. It is assumed that some parts of the intervention act unconsciously. Therefore an entire understanding of the underlying dependencies will not be possible. Moreover, it is decided to exclude male patients from participation - admittedly at the expense of generalization of the results. The reasons for this decision can be found in the low prevalence of AN in males. It has to be noted that there is a lack of standardized measures assessing DUI and DUC. This makes it necessary to develop a new measure for the purposes of the study. Additionally, the variables of interest mainly can only be assessed retrospectively. To counteract a possible distortion, self-reported data is reviewed in the telephone interview. In addition, it has to be considered that a prospective study would not be feasible due to the low prevalence of AN. There are some further limitations concerning the recruitment of the participants. There may be an adherence bias of the cooperating practitioners leading to different participation rates. There may be also a selection bias: Chronified patients with extremely low body weight may display a very long DUI but may be excluded due to their current physical status. The consequence may be an underestimation of the average DUI in the sample.

Since there hasn’t been a comparable intervention in the field of AN, some hypotheses have to stay exploratory. However, the effectiveness of public health interventions in general could be shown already (e.g. [31]). In the field of EDs the *psychenet* intervention and its evaluation will gain new knowledge about the DUI and factors influencing this period. Also, the successful implementation of a systemic intervention in this area will improve the networking of different health care professionals and facilitate patients’ flow into specialist care.

## Abbreviations

AN: Anorexia nervosa
BMI: Body-mass-index
CI: Confidence intervals
DUC: Duration until first contact with healthcare system
DUI: Duration of untreated illness
EDs: Eating disorders
BMBF: Federal Ministry of Education and Research
